The wound microbiome could play a key role in DFU outcomes, with microbial dysbiosis driving infection, worsening ulceration and ultimately resulting in major amputations or sepsis [13]. The beta-diversity of microbial samples can indicate differences in bacterial populations between patient samples or body sites, helping to understand variations in disease development or treatment responses [14]. Thus, the effect of PTA on changes in beta-diversity of the wound microbiome is yet not well understood [12, 15]. The microbiome composition as assessed by novel molecular (metagenomic) microbiological assessment may influence chronic infection and wound healing [16]. Current guidelines of the International Working Group on the Diabetic Foot (IWGDF) call for studies that provide new insights into these interactions [17]. PTA may alter the wound environment by enhancing oxygenation, potentially influencing the microbiome. However, restored blood flow might also lead to systemic changes, such as increased cytokine release or microbial translocation into the bloodstream [18, 19]. The role of molecular microbiological testing in guiding antimicrobial therapy and enhancing DFU outcomes requires further investigation [17]. Cell-free microbial DNA, released from infected tissues, is gaining attention as a potential biomarker for infection monitoring post-PTA [18, 19]. Results from this monocentric RCT study could guide the rational use of antibiotics and improve infection control following endovascular interventions in DFU persons. Biomarkers, such as endothelial proteins and apoptotic markers, may help diagnose ischemic DFU and predict outcomes, although their clinical utility remains unclear [20–22].

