This RCT will assess whether PTA within 48 h improves wound healing and reduces complications in participants with chronic ischemic DFUs over a 12-month period compared to standard care. The primary endpoint is the effect of early PTA on wound healing. Secondary endpoints include the combined occurrence of major adverse limb events (MALE), which serve as limb-specific outcomes, and major adverse cardiac events (MACE), which are considered safety-related secondary outcomes. Additional secondary endpoints include time to complete wound healing, major (above-ankle) amputation rate, and the need for new revascularization. Explanatory objectives are changes in wound microbiome composition and local microcirculation. The findings will inform the timing of PTA in managing DFS and help tailor more personalised and effective interventions for T2D persons. The study will also explore whether the baseline wound microbiome can predict healing outcomes.

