### Laboratory assessments

Venous blood samples in fasting state are processed immediately under standardised conditions, with comprehensive analyses conducted at the Central Laboratory of the University Hospital Düsseldorf as described [24]. Measurements include electrolytes, renal (creatinine, urea, cystatin C), liver function (ALT, AST, GGT, alkaline phosphatase, bilirubin), lipid profiles (cholesterol, triglycerides, HDL, LDL, Lp(a)), and glucose metabolism markers (HbA1c, insulin, glucose, C-peptide) to assess surrogates of whole-body insulin sensitivity, secretion (e. g. Homeostasis Model Assessment 2) and adipose tissue insulin resistance index [25]. Cardiovascular markers of myocardial damage, cardiac stress, and associated anaerobic metabolism (Troponin T hs, CK, CK-MB, NT-proBNP, lactate), markers of inflammations (CRP, procalcitonin, IL-6), diabetes autoantibodies (glutamate decarboxylase-, tyrosine phosphatase-, islet cell-, and zinc transporter-8-antibodies), erythropoiesis (erythropoietin, folic acid, vitamin B12, and reticulocytes) and iron metabolism (ferritin, transferrin, saturation, soluble transferrin receptor) are also measured. Thyroid function (TSH, free T4, free T3), bone health (25-hydoxy-vitamin D), blood coagulation (Quick, qPTT, fibrinogen, free haemoglobin), and haematological status (complete blood count) are evaluated. Anaemia measures include parameters of red blood cells turnover, formation, (dys)function, and haemolysis. Additionally, lactate and anaemia markers, including red blood cell function and iron status, are assessed to evaluate hypoxia and haemolysis.

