### Outcome monitoring

Over the 12-month follow-up period, MALE and MACE are monitored through patient interviews, focusing on vascular events (cardiac, cerebral, peripheral), amputations, infections, sepsis, hospitalisations, and all-cause mortality. For participants unable to attend on-site visits, telephone interviews are conducted to assess complications, including cardiovascular or all-cause mortality.

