One explanatory variable evaluates the effect of early PTA on wound microbiome dynamics. This objective aims to measure the beta-diversity changes of the wound microbiome, assessed via whole-genome sequencing and analysed using Bray–Curtis distances. In detail, taxonomic profiles from whole-genome sequencing of the wound microbiome will be generated using bioinformatics scripts. The sequencing data, produced via the Oxford Nanopore platform [36] will be analysed with Kraken2 [37] and minimap2 [38] based on a custom database including protozoan, fungal, and viral sequences. Visualisations for comparing metagenomic composition across taxonomic levels will be generated with custom scripts. Principal coordinate analysis based on Bray–Curtis distances will assess sample clustering, with the entire workflow provided as a reproducible Snakemake pipeline [39]. Effect sizes are based on expected changes in Bray–Curtis distances for beta-diversity. Nominal variables will be compared using the Chi-Square Test and Fisher's Exact Test where appropriate. Relationships between variables (e. g., changes in wound microbiome or local microcirculation and wound healing or complications) will be assessed using partial Pearson or Spearman correlation coefficients, with adjustments for confounders and multiple testing via the Bonferroni or Benjamini–Hochberg method. The standardised mean difference (Cohen's d) will be used for power analyses due to the lack of preliminary data on changes of ulcer area and combined incidence of MALE/MACE after early PTA. Changes in beta-diversity of the wound microbiome, will be analysed using Generalised Linear Mixed models with fixed effects including treatment group, bacterial taxa, time, and random effects to account for patient variability. Interaction terms will assess differential effects between treatment groups. The secondary endpoint includes combined MALE and MACE incidence post-angioplasty. Oxygen saturation in wound environment is measured as another explanatory outcome potentially linked to wound healing. Additional outcomes will include an evaluation of risk factors such as comorbidities (severity of anaemia and stages of chronic kidney disease), severity of insulin resistance, DSPN, the duration of hospital stay and interactions with medications, including antibiotics and antithrombotic therapies. Risk endpoints include the incidence of MALE, progression of diabetic complications (e.g., neuropathy), and hospital stay duration. These will be analysed using survival analysis methods and logistic regression to evaluate risk/benefit ratios. Multiplicity will be addressed as follows: The primary outcome will be analysed at a two-sided significance level of 0.05 without adjustment. For the prespecified family of confirmatory secondary outcomes, the family-wise error rate will be controlled at 0.05 using the Holm–Bonferroni procedure. For these outcomes, raw and adjusted p-values as well as corresponding adjusted 95% confidence intervals will be reported. Exploratory outcomes will not be adjusted for multiplicity and will be clearly identified as exploratory. Safety outcomes will be reported descriptively. The interaction effects of antibiotics, PTA timing, and concomitant antithrombotic treatments on both primary and secondary endpoints will be assessed using logistic regression models and subgroup analyses. Time-to-event clinical endpoints will be analysed with Kaplan–Meier survival curves, while covariate adjustments will be incorporated using Cox proportional hazards models. Correlation analyses (partial Pearson or Spearman coefficients) will account for confounders and include multiple comparison corrections via Bonferroni or Benjamini–Hochberg adjustments. Categorical variables will be compared using Chi-Square or Fisher's Exact Tests, while continuous variables will be analysed with Wilcoxon rank-sum tests or Student's t-tests, as appropriate. Two-tailed p-values below 0.05 will be considered statistically significant. Missing data will be summarised by variable, time point, and treatment arm, and patterns of missingness will be described graphically and statistically. The primary analysis will employ multiple imputation by chained equations (MICE; m = 20 imputations) under the assumption of missing at random (MAR). The imputation model will be specified to be congenial with the planned analysis and will include treatment arm, relevant baseline covariates (e. g., age, sex, ulcer duration, ulcer size, Wagner grade, HbA1c, infection status), and outcome variables. Continuous variables will be imputed using predictive mean matching, binary variables will be analysed via logistic regression, and ordinal variables will be analysed using proportional-odds models. Estimates will be combined using Rubin’s rules. Sensitivity analyses will include (i) complete-case analysis, (ii) best–worst and worst–best case scenarios, and (iii) a delta-adjusted pattern-mixture model to assess departures from MAR and exploring missing not at random (MNAR). All statistical analyses will be performed using the R Version 4.4 and SPSS for Windows 23.0 (SPSS Inc., Chicago, IL, USA). Figures are created with GraphPad Prism, Version 7.01 (GraphPad Software, Inc., La Jolla, CA, USA) or R, and Graphical abstracts using BioRender.com.

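### The risk/benefit list leaves out all-cause death and sepsis, although both are collected and death prevents or cuts short items on that list; whether they count in MALE/MACE is unsettled

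*Protocol article*

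**What the plan says.** Under Statistical methods and power calculation, the protocol article lists what enters its risk/benefit evaluation: "Risk endpoints include the incidence of MALE, progression of diabetic complications (e.g., neuropathy), and hospital stay duration". The next sentence assigns these to survival methods and logistic regression. Later in that section, clinical time-to-event endpoints get Kaplan-Meier curves and Cox models, and safety outcomes, which are not enumerated, are to be reported descriptively.

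The secondary endpoints are the combined occurrence of MALE and MACE plus three others: "Additional secondary endpoints include time to complete wound healing, major (above-ankle) amputation rate, and the need for new revascularization" (Background, repeated under Study design and randomisation protocol). The Background calls MALE limb-specific and spells out MACE as cardiac and safety-related. Neither composite has its components listed.

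Outcome monitoring says "MALE and MACE are monitored through patient interviews, focusing on vascular events", and the same sentence goes on to "amputations, infections, sepsis, hospitalisations, and all-cause mortality". For those who cannot attend, "telephone interviews are conducted to assess complications, including cardiovascular or all-cause mortality".

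The Background also raises a possible effect of the procedure itself: "restored blood flow might also lead to systemic changes, such as increased cytokine release or microbial translocation into the bloodstream".

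**The concern.** The trial compares two timings of the same procedure in a population at risk of sepsis and death. The list meant to weigh risk against benefit contains neither. The items it does contain are open to distortion by death: a participant who dies can no longer have a limb event, and a death in hospital ends the stay. If deaths differed between arms, the arm with more of them could look better on two of the three listed risk items, and nothing in the list would show why.

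The composite does not clearly repair this. Outcome monitoring suggests that sepsis and all-cause death belong to MALE/MACE surveillance, whereas the Background descriptions suggest that they do not belong to the endpoint. A reader cannot tell which secondary result, if any, would carry a difference in mortality.

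**Working it through.** **1. Lists side by side.**

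| Event | Outcome monitoring | Secondary endpoints | Risk endpoints |
|---|---|---|---|
| MALE | collected | in composite | named |
| MACE | collected | in composite | not named |
| Sepsis, infections | collected | not named | not named |
| All-cause death | collected | not named | not named |
| Hospital stay | hospitalisations collected | not named | duration named |

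**2. The two readings of Outcome monitoring.**
- (a) The collected events are composite components. Infections and hospitalisations would then be MALE/MACE events, which does not fit the limb-specific and cardiac descriptions in the Background.
- (b) They are only recorded alongside. Sepsis and non-cardiac death then belong to no named secondary or risk endpoint.

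The text does not decide between them. Under either reading, MALE alone is a listed risk endpoint and is described as limb-specific, so death competes with it whatever MACE contains. The same holds for major amputation and time to complete healing.

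**3. Size of the distortion in a logistic model for MALE.** The article gives no rates, so these are assumptions: 100 per arm, the same 30% of each arm would have MALE if all survived, and 5 (elective) v 10 (early) die before any MALE. Deaths are counted as event-free.
- If those who die carry the same 30% risk: elective 0.30 × 95 = 28.5 events, early 0.30 × 90 = 27.0. The proportions are 28.5% v 27.0%, a spurious advantage of 1.5 points for early PTA.
- If none of those who die would have had MALE: 30% v 30%, 0 points.
- If all would have: (30 − 5)% v (30 − 10)% = 25% v 20%, 5 points.

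**4. The stated sample size.** With d = 0.4, two-sided alpha 0.05 and 80% power, n = 2 × (1.960 + 0.842)² / 0.4² = 2 × 7.85 / 0.16 = 98.1, so 99 per group. The t-test version gives 99.1, so 100 per group. The stated 100 reproduces and does not bear on this point.

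**5. What 100 per arm can show for death or sepsis.** With p̄ the mean of the two risks, power = Φ[(|p1 − p2| − 1.96 √(2p̄(1 − p̄)/n)) / √(p1(1 − p1)/n + p2(1 − p2)/n)]. For 5% v 10%: (0.05 − 1.96 × 0.03725) / 0.03708 = −0.62, so power is 0.27. The 95% CI half-width is 1.96 × the square root in the denominator. All rates are assumed.

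| Risks | Power | CI half-width, points |
|---|---|---|
| 5% v 10% | 0.27 | 7.3 |
| 10% v 15% | 0.19 | 9.1 |
| 10% v 20% | 0.51 | 9.8 |
| 5% v 15% | 0.66 | 8.2 |

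These endpoints would serve estimation, not a powered test.

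**The case against.** The strongest reply is that this is a condensed article. Composite definitions, safety tables and the handling of death may be in the full protocol or analysis plan. The risk sentence is worded as open, and it omits MACE, which the article itself calls safety-related, so it is not the whole safety list. Descriptive reporting of safety outcomes gives sepsis and death a route into the results. All of this stands, and for that reason the absence of component definitions is not the point here. What the reply does not meet is that the article does enumerate its risk/benefit items and their methods, that death bears directly on two of them, and that its own sections pull apart on where death and sepsis belong. Descriptive reporting of unnamed outcomes does not put either into the risk/benefit evaluation.

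Four stronger inferences are tempting, and the documents do not support them.
- *That septic or non-cardiac deaths are censored in the composite.* No censoring rule is given. Outcome monitoring lists these events, and cerebral ones, under MALE/MACE, so the word cardiac cannot be taken as a component list.
- *That the plan identifies systemic infection as a harm of PTA.* The Background says only that restored flow might bring systemic changes, and it links sepsis to dysbiosis. The Discussion adds that delay may favour anaerobic growth and inflammation, so mechanisms are offered in both directions.
- *That a benefit on MALE/MACE would vanish once deaths are counted.* Any hazard ratio built for this would rest wholly on assumed rates and on reading (b).
- *That the inflammation markers should be compared between arms from V0 to V1.* V0 is recruitment and V1 is PTA plus 24 h. The interval is days in the early arm and up to about 6 weeks in the elective arm, so the contrast would mix reperfusion with elapsed time and care.

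**Conclusion.** The point holds in a limited form. All-cause death and sepsis are collected but named in neither the risk/benefit list nor the secondary list. Death competes with MALE, major amputation and healing and can shorten hospital stay, and the analyses described do not address this. Whether death and sepsis enter the composite is unsettled between the Background, Outcome monitoring and Statistical methods.

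The size cannot be fixed from the article. Under the assumptions shown, the spurious shift in the MALE proportion is 1.5 points, with a range of 0 to 5. It is nil if deaths are balanced and carry the same limb risk. The effect on hospital stay is possible but not shown, since a fatal admission can also be long. If the full protocol counts all-cause death in MACE, the composite is protected, but MALE, major amputation, healing and hospital stay are not. This should be corrected, but it does not threaten the primary endpoint or the sample size.

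**What to change.** - State whether sepsis or systemic infection and all-cause death are MALE/MACE components or separate safety outcomes, and bring the Background, Outcome monitoring and Statistical methods into line.
- Add all-cause death and sepsis or systemic infection to the risk/benefit evaluation, by randomised arm, as risk differences with 95% CIs labelled as estimation. Count from randomisation: visits are timed from PTA, so counting from PTA would leave out the elective arm's wait of up to 6 weeks.
- For MALE, major amputation and time to complete healing, and for the composite if it excludes all-cause death, report cumulative incidence with death as a competing event beside the Kaplan-Meier and Cox results.
- In logistic models, do not count participants who died without the event as event-free.
- Read hospital stay together with death, for example as days alive and out of hospital.

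The cost is some wording and a few extra tables from data already collected. Sample size, visits and treatment are unchanged.

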**Fig. 1 Fig1:**
[figure not shown]
Timeline. The figure shows follow-up visits at respective time points during the study period. The specified times of the respective follow-up examinations refer to the time after the PTA. PTA = Percutaneous transluminal angioplasty, PAD = Peripheral arterial disease, T2D = Type 2 diabetes, DFU = Diabetic foot ulcer, RCT = Randomised controlled trial

The primary endpoint of the PTA-DFS Study is to assess the effect of early PTA on wound healing in T2D participants and chronic ischemic DFU. Wound healing is measured by the reduction of 3D wound area, assessed using clinical grading and 3D-camera analysis with AI-based evaluation of wound length, width, and depth. The secondary endpoint is the combined incidence of MALE and MACE post-angioplasty between early and elective PTA treatment, time to complete wound healing, major amputation rate and the need for new revascularization. Explanatory variables for the primary endpoint are differences in quantitative shifts in bacterial taxa with different oxygen requirements (aerobes, anaerobes) (Fig. 2). These shifts post-PTA will be analysed using appropriate statistical methods, such as Generalised Linear Mixed Models (GLMMs), accounting for treatment group (early PTA vs. elective PTA), bacterial taxa, and time, with random effects to adjust for individual variability. Another explanatory variable for wound healing is the change in oxygen saturation in the wound environment, measured by multispectral near-infrared spectroscopy (NIRS). These outcomes will be analysed using Cox proportional hazard models using time-to-event outcome for MALE/MACE events, adjusting for baseline covariates to evaluate the effectiveness of early PTA compared to standard treatment.

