### Statistical methods and power calculation

The primary endpoint focuses on the difference in changes of wound area (delta wound area at first - last visit) in T2D participants after early PTA compared to individuals with standard PTA. For the primary—change in wound area after early PTA—and secondary endpoint—combined incidence of MALE and MACE—a power calculation was performed. Assuming a medium effect size (Cohen's d = 0.4), corresponding to 0.4 standard deviations of the difference in delta wound area and difference in time-to-event from baseline to last visit between groups, a sample size of n = 100 per group (total n = 200) is required to achieve 80% power at alpha = 0.05.

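### The confirmatory secondary family has its own 0.05 with no link to the primary, so the joint false-positive rate of confirmatory claims can reach at most 10% and a claim after a failed primary is not ruled out

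*Protocol article*

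**What the plan says.** The multiplicity rule stands in the protocol article under *Statistical methods and power calculation*, introduced by "Multiplicity will be addressed as follows". It has four parts.

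- Primary: "The primary outcome will be analysed at a two-sided significance level of 0.05 without adjustment".
- Secondary: "For the prespecified family of confirmatory secondary outcomes, the family-wise error rate will be controlled at 0.05 using the Holm–Bonferroni procedure".
- Reporting of that family: "For these outcomes, raw and adjusted p-values as well as corresponding adjusted 95% confidence intervals will be reported".
- Everything else: "Exploratory outcomes will not be adjusted for multiplicity and will be clearly identified as exploratory. Safety outcomes will be reported descriptively".

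The members of the confirmatory family are not itemised where the rule is given. *Background* names the combined MALE and MACE endpoint and then says: "Additional secondary endpoints include time to complete wound healing, major (above-ankle) amputation rate, and the need for new revascularization". The endpoint paragraph after Fig. 1 gives the same list. That makes four candidates.

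The power statement in the same statistical section covers both wound area and combined MALE/MACE, using a standardised effect of 0.4, 100 participants per group, 80% power and alpha 0.05.

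**The concern.** Holm–Bonferroni limits false positives inside the secondary family only. The primary has spent a full 0.05 before that family is opened, and the family then has another 0.05 whatever the primary result was. If the secondaries were described as supportive, two separate levels would be unremarkable. The article calls them confirmatory and sets them against the exploratory outcomes, so the rule offers two routes to a confirmatory statement about early angioplasty.

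At stake is how a mixed result is read. Suppose wound area shows no significant difference but one secondary, such as time to healing, passes Holm. Under the rule as stated, that secondary keeps its confirmatory label. The set of confirmatory claims then carries a false-positive rate above that of either tier.

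**Working it through.** **Inputs**

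- Primary: two-sided 0.05. Secondary family: 0.05 by Holm. Both from *Statistical methods and power calculation*.
- Family size: m = 4, assumed from the endpoint lists in *Background* and after Fig. 1.
- Correlations between test statistics: not given in the article, so a range is shown.

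**The plan's own figure first.** For d = 0.4, two-sided 0.05 and 80% power, n per group = 2 × (1.960 + 0.842)² / 0.4² = 98.1, so 99. The t-test version gives 99.08, so 100. The stated 100 per group is reproduced, and power at 100 per group is 80.4% (t-test). The sample size is right and corresponds to a two-sided 0.05 for the primary.

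**Bound without a correlation assumption.** The chance of at least one false confirmatory claim is at most 0.05 + 0.05 = 0.10.

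**Independent tests.** If the primary is independent of the family and the family uses its full 0.05, the rate is 1 − 0.95 × 0.95 = 0.0975. With four independent secondaries, Holm's first step is 0.05/4 = 0.0125 and the family's own rate is 1 − 0.9875⁴ = 0.0491. The joint rate is then 1 − 0.95 × 0.9509 = 0.0966, about 9.7%.

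**Correlated tests.** Simulation under the global null used one million draws per row of multivariate normal statistics with equal correlation. A claim was counted if the primary had p < 0.05 or the smallest of the four secondary p-values was below 0.0125.

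| Correlation | Any false confirmatory claim | Secondary claim with primary not significant |
|---|---|---|
| 0 | 9.7% | 4.7% |
| 0.3 | 9.2% | 4.2% |
| 0.5 | 8.4% | 3.3% |
| 0.7 | 7.1% | 2.1% |
| 0.8 | 6.4% | 1.4% |
| 0.9 | 5.5% | 0.5% |

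Repeat runs differ by about 0.1 percentage point. With a family of two, the joint rate is 8.6% at correlation 0.5 and 6.1% at 0.9.

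**Unequal correlations.** These are all assumed: primary with time to healing 0.3–0.8, primary with the other secondaries 0.1–0.4, among limb outcomes 0.15–0.7. The joint rate runs from 9.4% down to 8.0%, of which 4.4 down to 3.0 percentage points are secondary claims after a non-significant primary.

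**With a gate.** If the family is tested only after a significant primary, the joint rate under the global null equals the primary's rate, 5.0%. The control holds beyond that case. If the primary null is true, any confirmatory claim needs a false primary rejection (at most 5%). If it is not true, Holm limits false secondary claims to 5%.

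**The case against.** The strongest reply is that nothing the article states is broken. It gives two rates, 0.05 for the primary and 0.05 within the secondary family, and both hold as written. It never states a trial-wide 0.05. That stands: a reader might infer that the plan exceeds its own promised level, and the text does not support that. The 10% ceiling describes the joint rate and contradicts no stated figure.

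A second reply is that *Study protocol, data, and biosample handling* mentions a statistical analysis plan, which is not shown and could contain a gate without conflicting with any sentence of the article. This carries less weight. The article does not defer multiplicity; it sets out a tiered rule and calls the second tier confirmatory. If a gate exists elsewhere, the published rule is still incomplete in the respect that matters.

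Third, a reader might infer that the investigators intend to declare early angioplasty effective after a failed primary. No section says so, and wound area is named throughout as the single primary. The supportable statement is that the stated rule does not prevent such a claim.

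Fourth, a flat 8–10% would be too firm.

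- Wound-area change and time to healing describe the same ulcer, and *Outcome monitoring* follows amputations as part of MALE/MACE, so some correlations may be high.
- *Background* calls MACE safety-related, while safety outcomes are to be reported descriptively, so even the composite's place in the family is unclear.
- Fisher's exact test, which the article allows, is conservative for rare events. With 100 per arm and assumed event rates of 3–10%, its true size at the 0.0125 level is only about 0.1–0.6%.

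All of this pulls the rate down from the ceiling, which is why a wider range is given.

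Finally, the gate has a real cost, because MALE/MACE was included in the power calculation. That is accepted and is set out with the fix.

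**Conclusion.** The concern holds in a limited form. The rule gives confirmatory status to two tiers, each at its own 0.05, with nothing connecting them. The joint false-positive rate under the global null is at most 10%, about 9.7% with independent tests, and roughly 6–9% under positive correlation. Only near-perfect correlation throughout brings it close to 5% (5.5% at 0.9). The range rests on four secondaries, approximately normal test statistics and correlations that the article does not give; the 10% ceiling needs none of these.

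The primary analysis is unaffected: its error rate, power and sample size are as stated. This is a cheap improvement to a rule that is incompletely fixed, not a flaw in the main inference.

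**What to change.** Add one sentence to the multiplicity rule in *Statistical methods and power calculation*: the Holm family is tested confirmatorily only if the primary outcome is significant at two-sided 0.05; otherwise the secondary results are reported as supportive or exploratory, with estimates and confidence intervals. List the members of the family in the same place and say whether the MALE/MACE composite belongs to it. Dropping the word confirmatory for the secondaries would also resolve the point.

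The change needs no extra participants: the primary keeps its full 0.05, so 100 per group still gives 80.4% power. The cost is that no confirmatory secondary claim, including one on MALE/MACE, is available if the primary is not significant. At the assumed d = 0.4 that happens with probability 1 − 0.804 = 0.196, about 20%, and more often if the true effect is smaller. If the sponsor finds that too high a price for MALE/MACE, splitting one alpha between primary and family is an alternative, but it would lower the primary's level and so reduce its power at the present sample size.
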